## Abstract

**Background:**

Patients with incurable cancer have to deal with a wide range of symptoms due to their disease and treatment, influencing their quality of life. Nowadays, patients are expected to adopt an active role in managing their own health and healthcare. Oncokompas is an eHealth self-management application developed to support patients in finding optimal palliative care, tailored to their quality of life and personal preferences. A randomized controlled trial will be carried out to determine the efficacy and cost-utility of Oncokompas compared to care as usual.

**Methods:**

136 adult patients with incurable lung, breast, colorectal and head and neck cancer, lymphoma and glioma, will be included. Eligible patients have no curative treatment options and a prognosis of at least three months. Patients will be randomly assigned to the intervention group or the control group. The intervention group directly has access to Oncokompas alongside care as usual, while the waiting list control group receives care as usual and will have access to Oncokompas after three months. The primary outcome measure is patient activation, which can be described as a patient’s knowledge, skills and confidence to manage his or her own health and healthcare. Secondary outcome measures comprise self-efficacy, health-related quality of life, and costs. Measures will be assessed at baseline, two weeks after randomization, and three months after the baseline measurement.

**Discussion:**

This study will result in knowledge on the efficacy and cost-utility of Oncokompas among patients with incurable cancer. Also, more knowledge will be generated into the need for and costs of palliative care from a societal and healthcare perspective.

**Trial registration:**

Netherlands Trial Register identifier: NTR 7494. Registered on 24 September 2018.

## Background

Quality of life is an important aspect of healthcare for patients with incurable cancer. These patients have to deal with physical symptoms due to their disease and treatment, and often suffer from psychological, social and existential concerns, negatively affecting their quality of life [1–3]. Palliative care (or supportive care) for patients with incurable cancer focuses on reducing symptoms, improving quality of life and supporting patients and their families [4]. It not only concerns the management of physical symptoms related to the disease and its treatment. It also involves the provision of services to meet emotional, social, psychological, spiritual, informational, and practical needs [5–7]. Although there is evidence that early palliative care improves patients’ quality of life [8], palliative care services are often discussed at a late stage of the advanced cancer trajectory and many patients have unmet needs [9, 10].

Nowadays, patients are expected to adopt an active role in the management of their own well-being and healthcare [9, 10]. Self-management is defined as “those tasks that individuals undertake to deal with the medical, role, and emotional management of their health condition(s)” [11]. Research has shown that interventions supporting self-management can improve quality of life of patients with chronic disease and can be cost-effective [13–15]. They can also be beneficial for patients in terms of self-efficacy and patient activation [11, 16]. Evidence suggests that cancer patients with high self-efficacy are less likely to have negative psychological outcomes [17].

Patient activation can be described as a patient’s knowledge, skills and confidence to manage his or her own health and healthcare [18]. Research indicated that changes in activation are followed by changes in self-management behaviors [16] and that more activated patients are less likely to have unmet needs [19]. A study among patients with diabetes reported the positive relation between patient activation and self-reported health status across several studies [20]. Furthermore, a higher level of patient activation is associated with lower total costs from a healthcare and societal perspective [21]. Patient outcomes may be influenced by patients’ confidence to manage their disease and thereby lead to lower healthcare costs [22].

Self-management can be stimulated through the use of eHealth. A systematic review showed evidence for positive effects of eHealth on cancer patients’ knowledge levels and information competence, and possibly also on health status and quality of life [12]. Furthermore, eHealth has the potential to be cost-saving [23]. To the authors’ knowledge there is no clear evidence on the efficacy of tailored eHealth interventions supporting self-management in palliative care.

To support cancer patients in managing their well-being by informing them where they can find advice and guidance, the eHealth self-management application Oncokompas has been developed. This application helps patients to monitor their quality of life, using Patient-Reported Outcome Measures (PROMs), followed by automatically generated feedback and advice on palliative care services, tailored to their health status and personal preferences. The aim of the current study is to determine the efficacy and cost-utility of Oncokompas as a self-management instrument on patient activation, general self-efficacy, and quality of life among patients with incurable cancer (who are not yet in the terminal phase of their illness) compared to care as usual.

## Methods/design

### Study design

A prospective monocenter randomized controlled trial (RCT) with two parallel groups will be conducted among patients with incurable cancer to determine the efficacy and cost-utility of Oncokompas.

Patients will be randomly assigned to the intervention group or the waiting list control group. Patients in the intervention group will get direct access to Oncokompas alongside care as usual, while patients in the control group will receive care as usual and will be placed on a waiting list. This means that they will be given access to Oncokompas three months after the baseline measurement (i.e. after completion of the last questionnaire (t2)).

This study has been approved by the VUmc Medical Ethical Committee (registration number 2018.224). All respondents are informed that participation is voluntary. Respondents will provide written informed consent before inclusion. The flow diagram of the RCT is shown in Fig. 1. Figure 2 shows the schedule of enrollment, intervention and assessments (according to the Standard Protocol Items: Recommendations for Intervention Trials (SPIRIT)) (see Additional file 1).

**Fig. 1 Fig1:**
[figure not shown]
Flow diagram of the RCT

**Fig. 2 Fig2:**
[figure not shown]
The schedule of enrollment, intervention and assessments of the RCT (according to SPIRIT)

### Study population

#### Inclusion and exclusion criteria

This study will include adult patients (18 years or older) with incurable cancer (i.e. not having curative treatment options) who have a life expectancy of at least three months. Patients are included when they are diagnosed with lung cancer, breast cancer, colorectal cancer, head and neck cancer, lymphoma, or glioma. Furthermore, patients must be aware of the incurability of their cancer.

Patients are excluded when they have severe cognitive impairments or psychotic behavior (delusions and hallucinations), a poor understanding of the Dutch language (and thereby are not able to complete a Dutch questionnaire), or when they are too ill to participate. Patients are also excluded when they do not have access to the Internet or do not have access to an e-mail address, when their healthcare professional thinks that participation will be too much of a burden because a patient is already participating in other studies, or when they already used Oncokompas before (i.e. as cancer patient awaiting or undergoing curative treatment, or as cancer survivor).

### Study procedures

In various hospitals in the Netherlands, patients will be informed about this study by their healthcare professional. Patients eligible to participate will be approached by their medical specialist, (research)nurse or nurse specialist when they visit the outpatient clinic. Apart from informing and referring patients to the research team, no actions regarding the study will take place in the hospitals (therefore this study is marked as a monocenter study).

The coordinating researcher will further inform interested patients by phone or through direct face-to-face contact at the outpatient clinic. Patients also receive a letter with information about the study and Oncokompas. When patients want to participate, they sign the informed consent form. After the researcher has received the informed consent form, patients will receive a link to the online baseline questionnaire by e-mail. Patients who completed the baseline questionnaire (t0) will be randomized into the intervention group or the control group. Patients randomized in the intervention group will receive an invitation e-mail for Oncokompas through which they can activate their personal account. Patients randomized in the control group will receive an e-mail to activate their Oncokompas account after completion of the last questionnaire (t2). The other questionnaires will be sent two weeks after randomization (t1) and three months after the baseline measurement (t2).

#### Randomization

After completion of the baseline questionnaire, patients are randomly assigned to the intervention group or the control group, using block randomization. Blocks will have a length of four up to eight. Randomization takes place in a 1:1 ratio. The randomization scheme is created by a researcher not involved in the study, which also carries out the allocation of participants, using random allocation software (i.e. Sealed Envelope). Subsequently, this researcher notifies the coordinating researcher of the study about the outcome of the allocation after randomizing a participant. Blinding of the coordinating researcher is not possible since this researcher will send out the invitations for Oncokompas to patients and has to support patients during the study, for example when they have questions regarding technical issues.

### Intervention

Oncokompas is an eHealth self-management application that supports patients in finding and obtaining optimal palliative care, tailored to their health status, personal characteristics and preferences.

Oncokompas comprises three components: 1) Measure, 2) Learn, and 3) Act.

After the log-in procedure is completed, patients enter the first component of Oncokompas, ‘Measure’. This component starts with the completion of a general questionnaire. Based on the patient’s answers, Oncokompas selects the topics appropriate for this patient (e.g. when someone has no children, there will be no children-related topics). Subsequently, patients can select which topics they want to monitor within Oncokompas. Table 1 gives an overview of all the topics covered in Oncokompas. Patients complete Patient-Reported Outcome Measures (PROMs) on the topics they have chosen. Patients can complete PROMs targeting different domains of quality of life; physical, psychological and social functioning, and existential issues. PROMs were selected based on Dutch practical guidelines and literature searches, in collaboration with healthcare professionals and patients. The answers given to the PROMs are processed real-time and algorithms are used to link them to feedback in the ‘Learn’ component. All algorithms are based on available cut-off scores, Dutch practical guidelines and/or consensus by teams of experts.

**Table 1 Tab1:** Overview of all topics covered in Oncokompas for patients with incurable cancer

Domain	Topics
Physical	Body weight
	Daily functioning
	Diarrhea
	Dysphagia
	Dyspnea
	Fatigue
	Information about treatment options
	Appetite loss
	Lymphedema
	Mouth problems
	Nausea and vomiting
	Obstipation
	Pain
	Sexuality
	Skin problems
	Sleep problems
	Other side effects of medical treatment
Psychological	Cancer related anxiety (including fear of suffering and fear of dying)
	Coping with emotions
	Depression
	Tenseness
Social	Being single and cancer
	Choices concerning the end-of-life
	Loneliness
	Meaningful daily activities
	Patient-physician communication
	Social life
	Relationship with partner
	Relationship with (adult) children
	Work issues
Existential	Meaning of life
	Saying farewell

In the ‘Learn’ component, patients get an overview of their overall well-being on topic level, using a three-color system. A green score means that the patient is doing well on a topic, an orange score means that a topic could use attention and support, and a red score means that a topic needs attention and support. Patients get personalized feedback on their outcomes, tailored to their health status, personal characteristics and preferences. In addition, Oncokompas provides information on evidence-based interrelated symptoms (e.g. depression and sleeping problems). The feedback in the ‘Learn’ component concludes with comprehensive self-care advice, such as tips and tools, tailored to the individual patient.

In the ‘Act’ component, patients are provided with personalized palliative care options, based on their health status, preferences (e.g. preferences for individual therapy versus group therapy) and their neighborhood (e.g. Oncokompas shows the palliative care options the closest to the patient, based on a patient’s ZIP code). When patients have an orange score on a topic, the feedback includes suggestions for self-help interventions. When they have a red score on a topic, the feedback always includes the advice to contact their medical specialist, general practitioner, or a specialized healthcare professional (e.g. a physiotherapist or psychologist) [24].

Initially, Oncokompas was developed targeting cancer survivors [24–26]. From 2016 till 2018 Oncokompas has been extended to make the content of the application suitable for patients with incurable cancer, who are not yet in the terminal phase of their illness. The content of Oncokompas is developed in cooperation with patients, healthcare professionals and representatives of allied health services, using a stepwise, iterative, and participatory approach. This method actively involves users and other stakeholders in the design process [27].

### Care as usual

In this study, care as usual is defined as the care provided by the oncological team or by other healthcare professionals. This includes all medical and palliative care that patients receive, regardless of their participation in this study.

### Outcome assessment

The primary outcome measure to assess the efficacy of Oncokompas is patient activation. Secondary outcome measures are general self-efficacy and health-related quality of life. Also cost-utility outcomes will be evaluated. Outcome measures will be collected through online questionnaires at baseline (t0), two weeks after randomization (t1), and three months after the baseline measurement (t2).

An overview of the primary and secondary outcome measures is shown in Table 2.

**Table 2 Tab2:** Measurement overview

Aim	Outcome measures	Time point		
	*Instrument*	Baseline (t0)	Two weeks after randomization (t1)	Three months after baseline measurement (t2)
Efficacy				
*Primary outcome measure*	Patient Activation	X	X	X
	*Patient Activation Measure (PAM)*			
*Secondary outcome measures*	Self-efficacy	X	X	X
	*General Self-Efficacy Scale (GSE)*			
	Health-related quality of life	X	X	X
	*EORTC QLQ-C15 PAL*			
Cost-utility				
	Quality-adjusted life years	X		X
	*EuroQol 5 Dimensions (EQ-5D)*			
	Medical costs	X		X
	*iMTA Medical Consumption* * Questionnaire (iMCQ)*			
	Productivity costs	X		X
	*iMTA Productivity Cost Questionnaire (iPCQ)*			

### Primary outcome measure

#### Patient activation

Patient activation is measured with the Patient Activation Measure (PAM) [16, 26–29]. This questionnaire measures a patient’s self-reported knowledge, skills and confidence for self-management of his or her health or chronic condition [18]. The PAM consists of 13 items with a 4-point Likert scale on which patients can report their level of agreement (i.e. strongly disagree, disagree, agree, and strongly agree) or indicate that the item is not applicable. There are four levels of patient activation, ranging from the patients who hardly feel in charge of their own health (level one) to the patients who think they are well capable to manage their own health and healthcare (level four).

The total PAM score is computed by calculating the mean score of all the applicable items and transforming the mean score to a standardized activation score ranging from 0 to 100 [30]. Non-applicable items are not taken into account to calculate the mean score. Higher total PAM scores indicate a higher level of patient activation. The psychometric properties of the PAM 13-Dutch are generally good; the level of internal consistency is good (Chronbach’s alpha = 0.88) and item-rest correlations are moderate to strong [30].

### Secondary outcome measures

#### General self-efficacy

The General Self-Efficacy Scale (GSE) is a unidimensional questionnaire designed to assess how a person deals with difficult situations in his or her life. The GSE consists of 10 items with 4-point Likert scales ranging from 1 up to 4 (i.e. not at all true, hardly true, moderately true, and exactly true). The total score is calculated by adding up the scores on the 10 items, ranging from 10 to 40. A higher total GSE score indicates higher self-efficacy [31]. The psychometric properties of the GSE have been examined among participants from 25 countries; Cronbach’s alphas ranged from 0.76 to 0.90, with the majority in the high 0.80s [32].

#### Quality of life

Quality of life is measured by the European Organization for Research and Treatment of Cancer Quality of Life Questionnaire for cancer patients in palliative care (EORTC QLQ-C15-PAL). The EORTC QLQ-C15-PAL is an abbreviated 15-item version of the EORTC QLQ-C30 questionnaire. The EORTC QLQ-C15-PAL questionnaire is specifically designed for patients with advanced, incurable and symptomatic cancer with a median life expectancy of a few months [33].

The EORTC QLQ-C15-PAL comprises a global quality of life scale, two functional scales (physical and emotional functioning), two symptom scales (fatigue and pain), and four single items (dyspnea, insomnia, appetite loss, and constipation) [33]. All scales range in score from 0 to 100. A high score on the global quality of life scale represents a high quality of life and a high score on a functional scale represents a high or healthy level of functioning. A high score on a symptom scale indicates a high level of symptoms [34].

##### Cost-evaluation

A cost-utility analysis will be conducted comparing the difference in total three-month costs between the two study arms to the difference in Quality-Adjusted Life Years (QALYs) based on the EuroQol 5 Dimensions (EQ-5D).

#### EuroQol 5 dimensions

The EuroQol 5 Dimensions (EQ-5D-5L) asks respondents to describe their health state on five dimensions of quality of life (i.e. mobility, self-care, usual activities, pain/discomfort, and anxiety/depression). All those dimensions split into five levels. As a result, there are 3125 possibilities for one’s health status. The profile of answers that results after completing the questionnaire can be transformed to a given answer by the general public: the EQ-5D index using the Dutch index tariff. The EQ-5D also includes a visual analogue scale from 0 (worst health state) to 100 (best health state) on which respondents can represent their own health state. The EQ-5D is a validated instrument to measure health-related quality of life [35].

#### Medical consumption questionnaire and productivity cost questionnaire

An adapted version of the medical consumption questionnaire (iMCQ) and productivity cost questionnaire (iPCQ) will be used to measure the costs of healthcare (i.e. healthcare use and medication use), the costs for patients and their families (e.g. travelling costs and help received from family or friends), and costs within other sectors (e.g. productivity losses from paid work) in the previous three months. Both questionnaires are developed by the Institute for Medical Technology Assessment of the Erasmus University Rotterdam (iMTA), the Netherlands [36, 37].

#### Sociodemographic and medical data

Sociodemographic and clinical characteristics (i.e. age, gender, education level, and work situation) will be assessed at baseline (t0) using a study-specific questionnaire. Other characteristics (i.e. cancer type, treatment modality, and time since treatment) will be collected from the hospital information system, using a study-specific case report form.

### Sample size

To demonstrate the presence of an effect on the PAM between t0 and t2 of at least 0.5 standard deviations as statistically significant in a one-tailed test at alpha = 0.05 and a power of (1 - beta) = 0.80, at least 51 participants in each condition will be required at three months follow-up. Anticipating a dropout rate of 25% between t0 and t2 (based on earlier research in this population [38]), 68 participants per condition arm need to be included at baseline (t0). In total, 136 cancer patients will be recruited for this study.

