### Statistical analyses

All analyses will be conducted according to the intention-to-treat principle. Descriptive statistics will be generated to describe all sociodemographic and clinical characteristics, and outcome measures. To analyze whether randomization resulted in a balanced distribution of patient characteristics across the study arms, chi-square tests and independent samples t-tests will be used. When data is not normally distributed, Mann-Whitney U tests will be performed. In addition, independent samples t-tests will be used to test whether there are differences in outcome measures across study arms at baseline.

Linear Mixed Models (LMM) will be used to determine the efficacy of Oncokompas (e.g. changes in patient activation in the intervention group and the control group between t0, t1, and t2) by comparing longitudinal changes between both groups with fixed effects for study arm, time, and their two-way interaction, as well as a random intercept for subjects, and, if necessary, for referring hospitals. In case of baseline differences between study arms in sociodemographic and clinical characteristics, or outcome measures, the LMM analyses will be corrected for these differences. LMM will also be used to determine whether age, gender, socio-economic status (e.g. education level and work situation), cancer type, treatment modality, time since treatment, and baseline quality of life moderate the efficacy of Oncokompas. Fixed effects will be used for study arm, time, the potential moderator, and all two-way and three-way interaction effects, as well as a random intercept for subjects, and, if necessary, for referring hospitals.

Post-hoc analyses will be applied when significant results are found in the efficacy and moderation analyses mentioned above. Independent samples t-tests with Bonferroni correction will be used to measure the differences between the intervention group and the control group at follow-up measurements. To measure the effect sizes (ES) of the intervention, the (between group) Cohen’s d will be calculated. The magnitude of the ES is classified as large (≥ 0.80), moderate (0.50–0.79) or small (< 0.50) [39].

IBM Statistical Package for the Social Sciences (SPSS) version 26 (IBM Corp., Armonk, NY USA) will be used to perform all statistical analyses. All tests will be one-tailed. A *p*-value < 0.05 will be considered significant for all analyses.

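### The 80% power belongs to a single unadjusted one-tailed t-test, which is not how the plan decides efficacy; a Bonferroni-confirmed difference at three months has at most about 71%

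*Protocol article*

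**What the plan says.** The Sample size section of the protocol article targets "an effect on the PAM between t0 and t2 of at least 0.5 standard deviations", to be shown "as statistically significant in a one-tailed test at alpha = 0.05" with "a power of (1 - beta) = 0.80". From this it concludes that "at least 51 participants in each condition will be required at three months follow-up". It then adds an allowance ("Anticipating a dropout rate of 25% between t0 and t2") and arrives at 68 per arm, 136 in all. It mentions no correlation between repeated PAM scores, no expected effect at t1 and no multiplicity adjustment.

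The Statistical analyses section determines efficacy with a linear mixed model on t0, t1 and t2. The fixed effects are arm, time and their interaction, with a random intercept per patient. It continues: "Post-hoc analyses will be applied when significant results are found in the efficacy and moderation analyses mentioned above". The follow-up step is then described: "Independent samples t-tests with Bonferroni correction will be used to measure the differences between the intervention group and the control group at follow-up measurements". The section closes by making every test one-tailed at 0.05.

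**The concern.** The test behind the 51 per arm, an unadjusted one-tailed comparison at 0.05 for the three-month effect, does not appear in the Statistical analyses section as the efficacy decision. Efficacy is read from a model that also includes t1, and the arms are compared at individual visits only after a significant result and at a reduced alpha. If time is a factor, the interaction test has 2 df. It then has no direction, which conflicts with the statement that all tests are one-tailed. Each of these features can change the power, and the calculation takes account of none of them.

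At stake is whether the stated 80% applies to any test that will support the trial's conclusion about three-month patient activation.

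**Working it through.** **Inputs from the protocol article.** Effect 0.5 SD, one-tailed alpha 0.05, power 0.80, 51 per arm at t2, 25% dropout (Sample size); 1:1 allocation (Randomization); mixed model over three time points, then Bonferroni t-tests (Statistical analyses).

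**Assumed, not in the protocol article.** Bonferroni divisor 2 (tests at t1 and t2); time as a factor; compound symmetry with within-patient correlation ρ from 0.3 to 0.8; effect at t1 of 0, 0.25 or 0.5 SD; the 0.5 SD expressed in raw-score SD units.

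**1. The plan's own figure.** For a two-sample t-test the noncentrality is d·√(n/2), with 2n − 2 df. With n = 51 it is 0.5 × √25.5 = 2.525 on 100 df. At one-tailed 0.05 the critical value is 1.660 and the power is 0.806. With n = 50 the power is 0.799. So 51 is exactly the answer for this test, and 51 / 0.75 = 68. The arithmetic is right.

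**2. The planned t-test at t2.** Bonferroni over two follow-up visits gives 0.05 / 2 = 0.025, one-tailed. The noncentrality is the same, 2.525. The critical value becomes 1.984 and the power 0.706. This does not depend on ρ. A prior requirement for a significant model result can only lower it. To reach 80% on this test, 64 per arm at t2 are needed (power 0.801; 63 gives 0.795). That is 64 / 0.75 = 85.3, so 86 per arm at baseline.

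**3. The arm-by-time interaction with 2 df.** Under compound symmetry the noncentrality is λ = (n/2) · Σ(δⱼ − δ̄)² / (1 − ρ), where δⱼ is the arm difference at t0, t1 and t2. The reference distribution is F on 2 and 200 df.
- Differences of (0, 0, 0.5) or (0, 0.5, 0.5): Σ = 0.1667. At ρ = 0.5, λ = 25.5 × 0.1667 / 0.5 = 8.5 and the power is 0.738.
- Differences of (0, 0.25, 0.5): Σ = 0.125. At ρ = 0.5, λ = 6.375 and the power is 0.605.

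| ρ | t1 effect 0 or 0.5 SD | t1 effect 0.25 SD |
|---|---|---|
| 0.3 | 0.583 | 0.459 |
| 0.5 | 0.738 | 0.605 |
| 0.6 | 0.834 | 0.709 |
| 0.7 | 0.927 | 0.834 |
| 0.8 | 0.989 | 0.953 |

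If the 0.5 SD is meant in change-score units, the values are 0.605 to 0.738 whatever ρ is.

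**4. Both steps together.** The share of simulated trials with a significant interaction and then a Bonferroni-significant t2 test (51 complete per arm, 20,000 runs per scenario) was 41-51% at ρ = 0.3, 50-59% at 0.5, 63-68% at 0.7 and 69-70% at 0.8.

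**5. A single baseline-adjusted contrast at t2.** Adjustment divides the residual SD by a factor that turns d into d / √(1 − ρ²), tested on 99 df at one-tailed 0.05.
- ρ = 0.3: 0.5 / √0.91 = 0.524, noncentrality 0.524 × √25.5 = 2.647, power 0.837.
- ρ = 0.5: 0.5 / √0.75 = 0.577, noncentrality 2.915, power 0.894 (0.823 at one-tailed 0.025, equivalent to two-sided 0.05).

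**The case against.** The strongest reply is that the article makes the mixed model the means of determining efficacy. It places the t-tests under post-hoc analyses, where they measure differences. Nothing says that efficacy also requires a significant t2 t-test. This stands. A reader might infer that the plan delivers only some 50-71% power overall, but the protocol does not support that. The inference adds a success rule that is not stated. Its lower end also depends on the assumed correlation (about 41% at ρ = 0.3), and the interaction test alone exceeds 80% for every t1 effect considered once ρ reaches 0.7. If a Bonferroni-significant difference at either visit counted, with an equal effect at t1, the two-step path would reach 74-84% for ρ from 0.5 to 0.8 (68, 60 and 51 per arm at t0, t1 and t2, the 60 being assumed).

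Second, the 2 df are inferred. The article does not say how time is coded, and its one-tailed rule fits a 1-df contrast better. A one-sided t0-to-t2 contrast within the model would have about 72% at ρ = 0.3, 83% at 0.5 and 96% at 0.7 (same numbers per arm). This also stands, and it shows that the article leaves the deciding test open.

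Third, sizing on a t-test and analysing with a mixed model is common, and a full analysis plan may name the contrast. That lowers the severity. It does not remove the mismatch between two sections of the same article: the 80% is stated for an unadjusted test, while the only between-arm test described for t2 is gated and Bonferroni-corrected.

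**Conclusion.** The point holds as a mismatch between sizing and analysis, of moderate severity. It is not an arithmetic error: 51, 68 and 136 all reproduce.

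- Largely independent of outside assumptions: a Bonferroni-confirmed t2 difference has at most about 71% power with 51 per arm and 0.5 SD. This needs only a divisor of two.
- Dependent on assumptions: the interaction test may lie well below or well above 80%. The protocol article gives neither the correlation, nor the t1 effect, nor the SD to which the 0.5 refers, so its power cannot be stated as one figure.

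It would go too far to say that the trial is underpowered. What can be said is that the stated 80% is not shown for the analysis as described.

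**What to change.** Name one 1-df contrast as the primary test: the arm difference in PAM at t2, estimated from the mixed model with adjustment for baseline PAM. Test it directly, without an omnibus gate and without a Bonferroni split, and make t1 secondary. A 1-df contrast has a direction, so it also fits the one-tailed rule. State its power together with the assumed t0-t2 correlation: about 0.84 one-sided at 0.3 and 0.89 at 0.5 with 51 per arm.

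The cost is wording in the protocol and analysis plan, with no extra patients. The change should be fixed before the outcome data are analysed, so that the choice of contrast cannot appear data-driven. The downside is that an effect seen only at t1 can no longer carry the primary claim.

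If the present path is kept, the 80% should not be claimed for it. State instead that power for a Bonferroni-confirmed t2 difference is at most about 71%. Give the power of the mixed-model test with its degrees of freedom, assumed correlation and assumed t1 effect.
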